### Sample size calculation

Four hundred and fifty patients will be randomised to assessment by 4AT and 450 to
CAM. We will recruit sufficient patients to account for attrition, though we do not
expect significant attrition because the recruitment, consenting and assessment
process takes place over a small number of hours in a single episode. Of the 450
patients within each assessment arm, 15% (67) would be expected to have delirium. The
specificity of the triage tool would be estimated based on the 85% (383) without
delirium, while the sensitivity would be estimated from the 67 with delirium. Based
on the analysis using the normal approximation to the binomial distribution,
the two-sided 95% CI widths for the specificity and sensitivity would be as shown in
table 1 for a range of levels of diagnostic
test performance.

**Table 1 T1:** Precision of specificity, sensitivity estimation

Parameter	True level of parameter	95% CI width
Specificity	0.5	±0.050
Specificity	0.7	±0.046
Specificity	0.9	±0.030
Sensitivity	0.5	±0.120
Sensitivity	0.7	±0.110
Sensitivity	0.9	±0.072

It will therefore be possible to estimate the specificity precisely and the
sensitivity with moderate precision. The precision in estimating negative predictive
value would be expected to be similar to that for specificity; for positive
predictive value, it would be expected to be similar to that for sensitivity. For the
secondary objective of comparing 4AT and CAM, based on analysis by continuity
corrected χ^2^ test, we have 83% power to detect a difference in
specificity of 0.1, assuming a null hypothesis of specificity=0.70 for both
tests and a two-sided 5% significance level. The corresponding difference detectable
for sensitivity (null hypothesis sensitivity=0.7) would be 0.224 with 80% power.

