### Randomisation procedure

The allocation sequence will be created using computer-generated random numbers.
Participants will be randomised in a 1:1 ratio to be assessed using the 4AT or CAM
experimental assessment. The order in which they receive the reference standard and
experimental assessment will also be randomised in a 1:1 ratio. Randomisation will be
stratified by study site with block allocation. The randomised allocations will be
concealed until they are assigned, as the randomisation system will be
web based and requires a personal login and password. Once randomisation has
been performed, neither the researchers nor the participant will be blinded to the
allocation as both will be aware of the assessments conducted and the order in which
they are performed.

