#### Primary objective

(a) 4AT versus reference standard: the diagnostic accuracy of 4AT versus
the reference standard will be assessed using positive and negative predictive
values, sensitivity and specificity. The exact binomial 95% CI will be reported
for each measure. A ROC curve will be constructed to verify that the proposed cut
point of greater than 3 on the 4AT score is appropriate. The area under the ROC
curve and its 95% CI will be reported.

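### The 83% power for specificity and the 0.224 detectable difference in sensitivity do not follow together from the stated test and numbers, and the direction of the alternative is not given

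*Protocol article*

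**What the plan says.** All the planning figures are in the protocol article, under Sample size calculation. On arm size: "Four hundred and fifty patients will be randomised to assessment by 4AT and 450 to" CAM. On cases, of these 450 "patients within each assessment arm, 15% (67) would be expected to have delirium". On non-cases, the "specificity of the triage tool would be estimated based on the 85% (383) without" delirium.

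For the comparison of the two tools, the method is a chi-square test with continuity correction at a two-sided 5% level, with a null value of 0.70 for both tools. For specificity the text says "we have 83% power to detect a difference in" specificity of 0.1. The matching detectable difference "for sensitivity (null hypothesis sensitivity=0.7) would be 0.224 with 80% power". In neither case does it say whether the differing rate is above 0.70, below it, or whether the two rates lie either side of it.

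Under Secondary objectives in the Data analysis plan, the differences between 4AT and CAM are to be tested by Fisher's exact test and reported with a 95% confidence interval.

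**The concern.** A null rate and a difference do not fix the power of a two-proportion comparison. The variance depends on where the two rates lie, and at 0.70 it falls as the second rate rises and grows as it drops towards 0.5. With only 67 cases per arm this matters: direction alone moves power at a difference of 0.224 by almost 19 percentage points. A reader therefore cannot tell whether the quoted figures are cautious or hopeful. When the direction is supplied, the two figures turn out not to belong to the same calculation.

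The comparison with CAM is the first secondary objective, and sensitivity is its weak side. The detectable difference tells readers how large a gap in sensitivity the study could be expected to show, so it should be a figure that the design delivers.

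**Working it through.** **Inputs** (Sample size calculation; the 1:1 ratio is also under Randomisation procedure: "Participants will be randomised in a 1:1 ratio to be assessed using the 4AT or CAM").
- n = 383 per arm for specificity (85% of 450) and n = 67 per arm for sensitivity (15% of 450)
- null rate 0.70, two-sided 5%, continuity correction
- stated results: 83% power at a difference of 0.1; 0.224 at 80% power

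**Step 1: the article's own precision figures.** 1.96 × √(p(1−p)/n) gives 0.050, 0.046 and 0.030 for n = 383, and 0.120, 0.110 and 0.072 for n = 67, at p = 0.5, 0.7 and 0.9. All six entries of Table 1 reproduce, so 383 and 67 are the numbers in use.

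**Step 2: formula for the stated test.** With rates p1 and p2, d = |p1 − p2| and p̄ their mean,

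power = Φ{ [d − 1/n − 1.96·√(2p̄(1−p̄)/n)] / √([p1(1−p1) + p2(1−p2)]/n) }.

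**Step 3: specificity, n = 383, d = 0.1, 1/n = 0.0026.**
- 0.70 v 0.80: (0.1 − 0.0026 − 0.0613)/0.0311 = 1.160, power 87.7%
- 0.70 v 0.60: (0.1 − 0.0026 − 0.0676)/0.0343 = 0.870, power 80.8%
- 0.65 v 0.75: (0.1 − 0.0026 − 0.0649)/0.0329 = 0.987, power 83.8%

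**Step 4: sensitivity, n = 67, d = 0.224, 1/n = 0.0149.**
- 0.70 v 0.924: (0.224 − 0.0149 − 0.1323)/0.0647 = 1.187, power 88.2%
- 0.70 v 0.476: (0.224 − 0.0149 − 0.1667)/0.0828 = 0.512, power 69.6%
- 0.588 v 0.812: (0.224 − 0.0149 − 0.1552)/0.0768 = 0.702, power 75.9%

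**Step 5: solve the same formula for d at 80% power, n = 67, and set beside step 3.**

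| Alternative | Specificity power (stated 83%) | Detectable sensitivity difference (stated 0.224) | Power at 0.224 (stated 80%) |
|---|---|---|---|
| Above 0.70 | 87.7% | 0.206 (0.70 v 0.906) | 88.2% |
| Below 0.70 | 80.8% | 0.252 (0.70 v 0.448) | 69.6% |
| Centred on 0.70 | 83.8% | 0.235 | 75.9% |

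Turned round, 80% power at 0.224 needs about 56 cases per arm (above), 84 (below) or 74 (centred), against 67.

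**Step 6: does another method explain both figures?** Full enumeration of the corrected chi-square test gives specificity power of 87.9%, 80.9% and 84.0%, and detectable sensitivity differences of 0.202, 0.254 and 0.232 (above, below, centred). Fisher's exact test gives the same to within 0.1 percentage points of power, and the same detectable differences. Further variants were uncorrected, one-sided, unpooled variance, null-only variance and arcsine.
- Without the correction and centred, the sensitivity difference is 0.220 (0.222 with null-only variance), but specificity power is then 85.7% (85.5%).
- One-sided, corrected and below 0.70, the difference is 0.2245, but specificity power is 88.2%.
- The nearest to both is unpooled, corrected and centred: 84.1% for specificity and 77.7% at 0.224.

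No variant brings both figures within 2 percentage points of power, and the closest routes to 0.224 drop the correction or the two-sided level that the article states.

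**The case against.** The strongest reply is that little is at stake. The power statement serves a secondary objective, the result will be reported as a difference with its confidence interval, and the precision table for the primary objective is correct. Further, the article cites an earlier 4AT sensitivity of 89.7% and describes the CAM's sensitivity as satisfactory in trained hands. That makes an alternative above 0.70 the more plausible one, and there the stated figures understate what the design can do. All of this stands, and it limits the point to a text correction. It does not make 0.224 right, and it does not supply the missing direction.

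Several stronger readings are tempting, and the document does not support them.
- A reader might infer that the 83% is itself wrong. Taken alone it is within a point of the centred reading (83.8%), and the uncorrected test below 0.70 gives 82.8%. What fails is 0.224, and the two figures as a pair.
- A reader might infer that the real power for sensitivity is 70%. That needs 0.70 v 0.476, so one tool would miss more than half of cases. It is one end of a range, not the expected value.
- A reader might infer that the sentence beginning "The precision in estimating negative predictive" value is an error. It gives no figure and claims only similarity. On the rates of Table 1, negative predictive value is at least as precise as specificity throughout. Positive predictive value is clearly less precise than sensitivity only at 0.9/0.9 (±0.096 against ±0.072). The sentence is a loose approximation.
- A reader might see a conflict between the normal approximation in Table 1 and the analysis section's "The exact binomial 95% CI will be reported". The approximation is declared, the entries are correct for it, and planning with one and reporting with the other is ordinary practice.

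**Conclusion.** The point holds for the pair of power figures. Under the stated test, level and numbers, no direction of the alternative gives both 83% and 0.224, and 0.224 is not reached in any direction. The detectable difference is 0.206, 0.252 or 0.235 for an alternative above, below or centred on 0.70.

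The sign of the error depends on what the article leaves out. Above 0.70 both figures are conservative. Below 0.70 both are optimistic. Centred on 0.70, only the sensitivity figure is optimistic. The conclusion assumes exactly 383 and 67 per arm, with no loss and the 15% prevalence the article expects; it does not depend on choosing the formula over exact enumeration. The consequence is a misstated planning property of a secondary comparison. The primary objective is not affected.

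**What to change.** In Sample size calculation, give both rates for each comparison and recompute both figures with one named method. With the formula above, the text could state 88% power for specificity 0.70 v 0.80 and 80% power for sensitivity 0.70 v 0.906. The downward values would stand alongside: 81% for specificity 0.70 v 0.60, and 80% for sensitivity 0.70 v 0.448. If exact enumeration is preferred, the third decimal shifts (0.202 and 0.254 in place of 0.206 and 0.252), so the method should be named.

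The cost is a sentence or two of text. The sample size, Table 1, the predictive-value sentence and the planned analysis need no change on this account.

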### Data analysis plan

The detailed statistical analysis plan (SAP) will be agreed prior to database
lock and will be prepared by individuals blinded to the randomised allocations.

#### Primary objective

(a) 4AT versus reference standard: the diagnostic accuracy of 4AT versus
the reference standard will be assessed using positive and negative predictive
values, sensitivity and specificity. The exact binomial 95% CI will be reported
for each measure. A ROC curve will be constructed to verify that the proposed cut
point of greater than 3 on the 4AT score is appropriate. The area under the ROC
curve and its 95% CI will be reported.

#### Secondary objectives

4AT versus CAM: differences in each of sensitivity, specificity, positive
and negative predictive values between 4AT and CAM will be tested by
Fisher’s exact test and quantified by the difference in the two
proportions (4AT-CAM) and its 95% CI. To aid comparison of 4AT and CAM, the
overall performance of each will also be summarised using Youden’s
Index (sensitivity minus false positive rate) and the OR of sensitivity to
specificity.Performance of the 4AT cognitive screening items: Is the 4AT an adequately
sensitive tool for detecting general cognitive impairment as judged against
a documented history of dementia and/or the IQCODE? This objective will be
addressed using the same methods as for the primary objective.4AT versus clinical outcomes: as assessment of criterion validity, we will
assess the performance of the 4AT in predicting length of stay,
institutionalisation and mortality up to 12 weeks. Descriptive
statistics of clinical outcomes will be presented for the groups with and
without 4AT scores above the cut point of 3. The relationship between 4AT
and each of mortality and institutionalisation will be analysed via logistic
regression modelling; Kaplan-Meier curves and the Cox proportional hazards
model will be used to assess 4AT as a predictor of hospital length of stay.
The logistic regression and Cox models will adjust for age, gender and
presence of dementia.Individual items: we will conduct analyses examining performance of
individual items of the 4AT, for example, is altered level of
alertness alone a good predictor of delirium diagnosis? (methods as per
primary objective);Delirium severity: we will assess the 4AT total score as a measure of
delirium severity by calculating the Spearman correlation between 4AT and
DRS-R98 scores and its 95% CI.

Full details of the proposed statistical analyses for the primary objective and
secondary objectives (a)–(e) will be documented in a SAP which will include
details of methods for calculating derived variables, any sensitivity and subgroup
analyses and approaches to testing the assumptions in the statistical analyses.
The SAP will outline the plan for validation of the statistical analysis.

Individuals with missing data for the reference diagnostic test will be removed
from formal statistical analysis. Where any items of the CAM or 4AT were not able
to be assessed, an overall delirium diagnosis will still be derived where possible
based on the items which have been recorded. There will be no other imputation of
missing delirium diagnoses.

(f) Delivery costs of the triage tools: we will estimate the delivery costs
and subsequent resource consequences associated with the triage tools as a
function of sensitivity and specificity from the perspective of the UK National
Health Service (NHS). Potential resource consequences may include
additional diagnostic procedures (eg, more detailed cognitive screening and brain
imaging), altered management as well as readmissions. Healthcare resource use will
be derived from medical records, including the ‘TrakCare’
(InterSystems Corporation, Cambridge, Massachusetts, USA) electronic patient
record system, where available, as well as via patient or carer self-report.
Monetary values will be attached to resource use, training and labour costs as
well as the indirect costs of delivering each diagnostic tool using standard NHS
pay and price estimates. Generalised linear models will be used to analyse
12 week cumulative costs which will inform longer term resource
consequences within a decision analytic model.

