## Methods and analysis

### Study overview

Nine hundred patients aged 70 or over in EDs or acute general medical wards
will be recruited in three sites (Edinburgh, Bradford and Sheffield). Study
recruitment commenced on 19 October 2015. Recruitment was planned to be
completed in December 2016, with final follow-up data collection and locking of the
database in March 2017. The assessments are: (a) a reference standard delirium
assessment lasting up to 20 min and (b) either the 4AT or the CAM lasting up
to 10 min. The reference standard and 4AT or CAM assessments will take place
within a maximum of 2 hours of each other, with a target interval of
15 min. The results of the reference standard assessment were recorded in the
case notes and communicated to the clinical team after the index assessments had been
completed and recorded. The team will invite an appropriate informant to complete a
questionnaire on participant’s preadmission cognitive function. This will be
completed within 4 weeks of the patient being recruited to the study assuming an
appropriate individual is available.

At 12 weeks, the team will also administer a 10 min resource-use questionnaire
(face to face in hospitalised patients or by telephone when possible) and will access
each recruited patient’s medical records at 12 weeks to ascertain a set of key
clinical outcomes, including length of stay, institutionalisation and mortality, as
well as to derive further information on resource utilisation. The study
flow chart is shown in figure 1. The study has been registered: international standard randomised
controlled trial number (ISRCTN) 53388093. UK Clinical Research Network ID:
19 502.

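### The 4AT v CAM comparison uses an unstratified Fisher's exact test: valid but conservative, about 3 to 8 points short of an uncorrected test's power for sensitivity, and without the site stratum used to randomise

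*Protocol article*

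**What the plan says.** Under Data analysis plan, Secondary objectives, the article tests the 4AT v CAM differences in sensitivity, specificity and both predictive values by "Fisher’s exact test and quantified by the difference in the two" proportions (4AT minus CAM) with a 95% CI. Neither the test nor the interval mentions site, and the method for the interval is not named.

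Under Randomisation procedure, "Participants will be randomised in a 1:1 ratio to be assessed using the 4AT or CAM", and the sequence is "stratified by study site with block allocation". Study overview names three sites.

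Under Sample size calculation, "Four hundred and fifty patients will be randomised to assessment by 4AT and 450 to" CAM. Of each arm, "15% (67) would be expected to have delirium", and specificity is "estimated based on the 85% (383) without" delirium. Power for the "secondary objective of comparing 4AT and CAM, based on analysis by continuity" corrected chi-square test is given as 83% for a specificity difference of 0.1 and 80% for a sensitivity difference of 0.224, both around 0.70 at two-sided 5%.

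Derived variables, sensitivity and subgroup analyses and assumption checks are left to a SAP that is not shown. The main test for this comparison is named in the article itself.

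**The concern.** Three features of the stated analysis prompt the question.

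- The allocation uses site as a stratum and the analysis does not.
- Fisher's test conditions on both margins and is known to be conservative in small tables. Sensitivity rests on only about 67 patients per arm and is the least informed comparison in the study.
- A Fisher p-value beside an interval for a difference in proportions can give conflicting answers, depending on how the interval is built.

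At stake is some power to distinguish the two tools on sensitivity, and a clean reading of p-value and interval together. The validity of the comparison is not at stake.

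**Working it through.** **Inputs.** From Sample size calculation: 67 with and 383 without delirium per arm, two-sided 5%, reference level 0.70. From Randomisation procedure and Study overview: 1:1 allocation, stratified by three sites. Assumed, because the article does not give them: about equal numbers per site (22 to 23 delirious patients per arm per site), and any between-site differences.

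**1. The plan's own figures.** Power = Φ[(d − c/n − 1.96·s0)/s1], where s0 = √(2p̄(1−p̄)/n), s1 = √([p1(1−p1)+p2(1−p2)]/n), and c = 1 with the continuity correction or 0 without.

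- Sensitivity, n = 67, d = 0.224 centred on 0.70 (0.588 v 0.812): s0 = √(2×0.7×0.3/67) = 0.0792 and s1 = √((0.2423+0.1527)/67) = 0.0768.
  - Uncorrected: (0.224 − 0.1552)/0.0768 = 0.896, power 81.5%.
  - Corrected: (0.224 − 0.0149 − 0.1552)/0.0768 = 0.702, power 75.9%.
- The article does not state the direction of the alternative. With the correction, power is 88.2% for 0.70 v 0.924 and 69.6% for 0.70 v 0.476. The stated 80% lies inside that range.
- Specificity, n = 383, 0.65 v 0.75, corrected: 83.8%, against the stated 83%.

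**2. True size at 67 per arm** (full enumeration, both arms at the same sensitivity):

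| Sensitivity | Fisher | Uncorrected chi-square |
|---|---|---|
| 0.70 | 3.3% | 5.0% |
| 0.80 | 3.1% | 4.9% |
| 0.90 | 2.4% | 5.1% |

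**3. Power for sensitivity at 67 per arm** (full enumeration, no site term):

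| Comparison | Fisher | Corrected chi-square | Uncorrected chi-square | Gap, Fisher to uncorrected |
|---|---|---|---|---|
| 0.70 v 0.924 | 90.3% | 90.3% | 93.4% | 3.1 |
| 0.588 v 0.812 | 76.8% | 76.8% | 82.0% | 5.2 |
| 0.70 v 0.90 | 79.2% | 79.2% | 84.4% | 5.2 |
| 0.70 v 0.476 | 69.1% | 69.1% | 74.8% | 5.7 |
| 0.90 v 0.75 | 55.9% | 55.9% | 63.8% | 7.9 |

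The whole gap appears with no stratification in either test. Fisher's power equals that of the continuity-corrected test.

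**4. Specificity at 383 per arm.** Fisher v uncorrected: 84.0% v 85.8% (0.65 v 0.75), 87.9% v 89.5% (0.70 v 0.80) and 81.0% v 82.9% (0.70 v 0.60). The gaps are 1.6 to 1.9 points.

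**5. What site adds** (simulation, three sites, 67 per arm; CMH = Cochran-Mantel-Haenszel, stratified by site):

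| Site differences (assumed) | Comparison | Fisher | Uncorrected, pooled | CMH, uncorrected | CMH, corrected |
|---|---|---|---|---|---|
| None | 0.70 v 0.476 | 69.5% | 75.0% | 75.0% | 69.2% |
| None | 0.70 v 0.924 | 90.2% | 93.2% | 93.3% | 89.7% |
| ±1 log-odds | 0.70 v 0.476 | 70.4% | 76.4% | 81.7% | 75.9% |
| ±1 log-odds | 0.70 v 0.924 | 91.2% | 94.2% | 95.1% | 92.0% |

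With similar sites, stratifying adds about nothing, and a corrected CMH test recovers nothing over Fisher. At offsets of ±0.5, stratifying adds 0.3 to 2.1 points. At ±1 (site sensitivities about 50%, 73% and 88%) it adds about 1 to 5 points with the average held at its nominal value. If the offsets are applied without holding the average, the ±1 gain reaches about 7 points for the downward alternative.

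**6. Type I error when sites differ.** At sensitivity 0.70, pooled Fisher falls to 2.9% at ±0.5 and 2.2% at ±1. Uncorrected CMH stays at about 4.8% to 5.1%, including at sensitivity 0.90.

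**7. Test against interval.** The interval method is not named, so two common ones are taken as assumptions. Fisher at 5% and the 95% CI disagree on significance in 10.4% (Wald) or 7.9% (Newcombe) of trials for 0.90 v 0.75, and in 6.7% or 5.3% for 0.70 v 0.90.

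**The case against.** The best defence is that Fisher's test is a standard, valid choice, in keeping with the exact intervals planned for the primary objective. It has the same power as the continuity-corrected chi-square named for the sample size, so analysis and planning test agree. That stands: nothing is lost against the named planning test. The gap is against what the same data could deliver.

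A second defence is that the unseen SAP may add a site-adjusted analysis. That also stands, but the article already fixes the main test.

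A third is that the stratified test is asymptotic. At sensitivity 0.90, 22 to 23 patients per arm per site leave only about 2 missed cases per cell. This is a real limitation, although the simulated type I error held.

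Two stronger readings are tempting and are not supported.

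- A reader might infer that ignoring site stratification is what costs the 5 or so points. It is not: a pooled uncorrected test recovers them, and the article gives no between-site variation in case mix, raters or accuracy from which a further loss could be claimed.
- A reader might infer that an analysis not matching the randomisation is invalid. Here pooling makes the test more conservative. It does not bias the comparison or inflate type I error.

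The conflict between test and interval is likewise a possibility under assumed methods, since the article does not name the interval method.

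**Conclusion.** The point holds as an efficiency matter on a secondary objective. Fisher's test is valid, and its conservatism costs about 3 to 8 points of power for sensitivity at 67 per arm, but under 2 points for specificity. This rests on the article's 15% prevalence and on the pairs of sensitivities shown.

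The omission of site is a separate and smaller matter. Its cost is about nil if sites are alike, up to about 2 points at an assumed ±0.5 log-odds, and roughly 1 to 7 points at ±1, depending on the alternative. The documents do not show which case applies. Priority is modest.

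**What to change.** In the SAP, before database lock:

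- Test sensitivity and specificity, 4AT v CAM, by a Cochran-Mantel-Haenszel test stratified by site, without continuity correction.
- Report the Mantel-Haenszel risk difference (4AT minus CAM) with its 95% CI from the same stratified analysis, and name the interval method. Test and interval will then be closely aligned.
- Use an exact or mid-P stratified version for sparse tables.
- Keep Fisher's exact test as a sensitivity analysis.

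The cost is wording only, with no change to sample size or data collection. The downside is reliance on an asymptotic test with small cells per site when sensitivity is near 0.90, which the exact or mid-P version covers. Dropping the correction departs from the planning test, but in the direction of more power than planned.

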screening and delirium screening, we also reviewed the broader literature on brief
tests for general cognitive impairment (including dementia). In the context of
designing a screening tool for the acute hospital, it is important to note that
delirium generally causes cognitive impairment detectable on the kinds of tests used
for dementia screening.^36 37^ Therefore,
abnormal test results may indicate delirium and/or dementia (as well as other causes
of cognitive impairment, such as learning disability).

It is clinically essential to know if any such impairment is acute, that is,
delirium, but also important to identify underlying general (acute or chronic)
cognitive impairment. A tool designed exclusively to detect cognitive impairment will
not lead to delirium detection without another step, and a tool designed only to
detect delirium may miss general cognitive impairment. In this light, we decided that
the 4 ’A’s Test (4AT) should include cognitive screening
sensitive to general cognitive impairment, but also including items on altered level
of alertness and change in mental status, both of which are strong indicators of
delirium.

The first version of the 4AT was drafted and tested informally by colleagues, changes
were made based on feedback and updated versions were tested again. After
several iterations involving 20 doctors and nurses of varying levels of experience,
the final version was produced. An initial audit in 30 inpatients comparing clinical
use of 4AT with independent reference standard DSM-IV assessment found 100%
sensitivity (CI 69% to 100%) and 90% specificity (CI 68% to 99%). A subsequent
validation study in Italy involving 234 consecutively recruited older hospitalised
patients found that the 4AT had a sensitivity of 89.7% and a specificity
of 84.1% for delirium.^38^ The area under
the receiver operating characteristic (ROC) curves for delirium diagnosis was
0.93. Since the 4AT was launched, locally and through the www.the4AT.com website,
it has been adopted in clinical units in several centres in the UK and
internationally.

Thus, in 2014, there was encouraging evidence that the 4AT has value as a tool for
delirium detection in routine practice. This evidence came from several sources: one
published study, audits in several sites, informal feedback, adoption in clinical
practice by several clinical units globally and a recent web-based survey focused
specifically on 4AT provided evidence supporting its use. Since this study was

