### Reference standard assessment

Reference standard assessment: this will be centred on the Delirium Rating
Scale-Revised-98 (DRS-R98),^45^ requiring
inspection of case notes, speaking to staff who know the patient or speaking to the
patient’s relatives or others who know them (with patient consent). As per the
instruction manual, the DRS-R98 will be supplemented by short neuropsychological
tests of attention and other domains, including Digit Span,^27^ the Observational Scale for Level of Arousal,^46^ the Richmond Agitation Sedation Scale^47^ and the DelApp objective attentional
assessment.^48^ We will also perform simple
orientation questions and record any formal prior diagnosis of dementia and
IQCODE^49^ scores. The DRS-R98 and supporting
tests will be used to inform a binary ascertainment of delirium based on DSM-IV
criteria. The final DSM-IV ascertainment of delirium will be based on a standardised
process with final verification by the chief investigator, blind to the 4AT or CAM
results. The panel of supporting tests, and the way the data are coded will be
designed such that the performance of the 4AT can also be evaluated against the DSM-5
criteria.^2^ The reference standard assessment
will take approximately 15–20 min.

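### The 4AT-CAM difference in specificity is planned without adjustment for recorded prior dementia, which forgoes a modest and nearly free gain in precision

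*Protocol article*

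**What the plan says.** Under Data analysis plan, Secondary objectives, the 4AT-CAM differences in sensitivity, specificity and predictive values are tested by Fisher's "exact test and quantified by the difference in the two" proportions and its 95% CI. No covariate or stratum enters. The same section adjusts the models for mortality, institutionalisation and length of stay for age, gender and dementia.

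Under Randomisation procedure, allocation is 1:1 and "stratified by study site with block allocation". Dementia is not a stratification factor.

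Under Reference standard assessment, which every patient undergoes, the researchers will perform "orientation questions and record any formal prior diagnosis of dementia and" IQCODE scores.

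Under Rationale for the study, the authors note of cognitive screening tests that "abnormal test results may indicate delirium and/or dementia (as well as other causes" of cognitive impairment).

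Under Coding and recording assessments, 4AT items 2 and 3 score up to 2 each, and a total of 4 or more is classed as delirium.

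Under Sample size calculation, the "specificity of the triage tool would be estimated based on the 85% (383) without" delirium, and "we have 83% power to detect a difference in" specificity of 0.1 around a null value of 0.70, by a continuity-corrected chi-square test at a two-sided 5% level.

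**The concern.** Specificity is the better-powered half of the only randomised comparison of the tools: 383 patients per arm, against 67 for sensitivity. A non-delirious patient with dementia who scores 2 on each cognitive item reaches a 4AT total of 4, and so is a false positive, with no altered alertness and no acute change. If dementia predicts false positives in this way, part of the variance of the crude specificity difference is explainable by a characteristic that precedes randomisation and is already collected. A chance imbalance in dementia between the arms would also shift the crude estimate in the trial actually run.

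At stake is some precision in the figure that the article says should help clinicians choose between tools. Specificity also feeds the cost analysis.

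**Working it through.** **Inputs from the Protocol article.** 450 patients per arm; 85% without delirium, so 0.85 × 450 = 382.5, stated as 383; null specificity 0.70; difference 0.10; continuity-corrected chi-square; two-sided 5%; stated power 83%.

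**Inputs assumed, because the article does not give them.** Dementia prevalence q among non-delirious patients: 10%, 20%, 30%. Gap g in specificity between patients without and with dementia: 0.1 to 0.4.

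**Step 1: reproduce the stated power.** Centre the rates on 0.70, giving 0.65 v 0.75, with n = 383.
- Corrected difference: 0.10 − 1/383 = 0.0974.
- Critical value: 1.96 × √(2 × 0.70 × 0.30 / 383) = 0.0649.
- SE under the alternative: √((0.65 × 0.35 + 0.75 × 0.25)/383) = √(0.415/383) = 0.0329.
- Power = Φ((0.0974 − 0.0649)/0.0329) = Φ(0.987) = 83.8%.

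This agrees with the stated 83%. Other readings are further off: corrected, 0.70 v 0.80 gives 87.7% and 0.70 v 0.60 gives 80.8%.

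**Step 2: variance removed by standardising for dementia.** If both tools lose g in specificity with dementia, each arm's binomial variance falls by q(1 − q)g². The proportional cut is 2q(1 − q)g² / 0.415. For q = 0.2 and g = 0.3:
- 2 × 0.16 × 0.09 / 0.415 = 0.0288/0.415 = 6.9%.
- SE ratio √(1 − 0.069) = 0.965, so the SE falls by 3.5%.
- Equivalent sample size 383/0.931, about 412 per arm. Step 1 at that n gives 86.5%.

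If only the 4AT is affected, the saving arises in one arm. Half of it is lost because the effect then differs by dementia status and the standardising weights come from the 766 sampled patients. The net cut is q(1 − q)g²/2 over 0.415. In the middle case this is 0.0072/0.415 = 1.7%.

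| q | g | Variance cut, both tools | Equivalent n per arm | Power | Variance cut, 4AT only |
|---|---|---|---|---|---|
| 10% | 0.1 | 0.4% | 385 | 84.0% | 0.1% |
| 10% | 0.4 | 6.9% | 412 | 86.5% | 1.7% |
| 20% | 0.3 | 6.9% | 412 | 86.5% | 1.7% |
| 30% | 0.4 | 16.2% | 457 | 89.9% | 4.0% |

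**Step 3: chance imbalance.** The SD of the between-arm difference in dementia prevalence at q = 0.2 is √(2 × 0.2 × 0.8 / 383) = 0.029. With g = 0.3, a 1-SD imbalance moves the crude difference by 0.3 × 0.029 = 0.009, and a 2-SD imbalance by 0.017, against a crude SE of 0.033.

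**Step 4: simulation.** 40,000 trials with q = 0.2, g = 0.3 in both arms and a true difference of 0.100.
- Over all trials the crude and standardised estimates both averaged 0.100.
- The variance cut was 6.8%, in line with step 2.
- Imbalance above 5 points in either direction occurred in 7.8% of trials.
- Where the arm with the higher specificity had more than 5 points more dementia, the crude difference averaged 0.080 and the standardised one 0.099.

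**The case against.** The strongest reply is that nothing here is wrong. Under concealed 1:1 randomisation the crude difference is unbiased, and its CI already allows for chance imbalance in dementia as in any other factor. Design and analysis match: power was set on an unadjusted test, the analysis is unadjusted, and the stated 83% reproduces. This stands. A reader might infer that the planned result is biased or its interval invalid. The article does not support that, and step 4 shows the opposite.

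A reader might also infer that the plan itself says dementia makes both tools falsely positive. It does not. The sentence in the Rationale concerns cognitive tests, not the binary 4AT or CAM result. 4AT scores of 1 to 3 are meant to capture impairment without delirium, and the CAM requires both acute change and inattention. The item scoring makes the mechanism plausible for the 4AT. For the CAM the article states none, so the smaller figures in the last column of the table must be taken seriously.

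Nor is it inconsistent to adjust the outcome models and not this comparison. The relation of 4AT score to mortality or length of stay is not randomised, so dementia is a potential confounder there. Randomisation removes that reason here. Only the efficiency argument remains.

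Finally, the comparison is secondary, and details such as sensitivity analyses are deferred to a SAP that is not shown and may already include an adjusted analysis. That lowers the weight of the point. But the article does fix the main method, and a more efficient estimate of the same marginal difference is available from data already collected.

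Extending the adjustment to sensitivity would not be sound. Only 67 delirious patients per arm inform it. At a sensitivity of 0.9 that is 67 × 0.1, or about 7 false negatives per arm, too few for a model with arm, dementia and age.

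**Conclusion.** The point holds as a modest efficiency gain for specificity only. At the protocol's own planning values (0.70, difference 0.10, 383 per arm), adjusting for prior dementia would cut the variance by about 0.4% to 16% if dementia affects both tools, raising power from 83.8% to between 84.0% and 89.9%. The middle case is about 7% and 86.5%. If dementia affects the 4AT alone, the cut is about 2% in the middle case and 4% in the largest. Adjustment would also protect against the occasional sizeable imbalance.

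All of these sizes rest on the assumed prevalence and gap, which the article does not supply. They cover dementia only; no gain from age was calculated. The unadjusted analysis remains valid, and the stated power is not in question.

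**What to change.** Before database lock, pre-specify in the SAP, for specificity only, a marginal (standardised) 4AT-CAM risk difference with 95% CI, from a logistic model with arm, documented prior dementia diagnosis and age. Report it alongside the crude difference and Fisher's test, which stay as planned. It targets the same marginal difference.

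Use the documented diagnosis, not the IQCODE: the diagnosis precedes randomisation, whereas the IQCODE depends on an available informant and may be completed up to 4 weeks after recruitment. Leave sensitivity unadjusted, or label any adjusted estimate of it exploratory.

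The cost is a few lines of SAP text and a small modelling step. No new data are needed.
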